## Abstract

**Background:**

Post-thoracic surgery pain remains a major clinical challenge, with substantial impact on pulmonary function, postoperative recovery, and patient quality of life. Thoracic epidural analgesia is widely regarded as the standard of care; however, it is associated with potential complications, including hypotension, urinary retention, and inadequate analgesia in a subset of patients. Intercostal cryoanalgesia, a peripheral nerve block technique that induces temporary axonal degeneration through controlled freezing, has emerged as a potential alternative for prolonged postoperative pain control.

**Objective:**

The primary objective of this study is to compare postoperative hospital length of stay between intercostal cryoanalgesia and thoracic epidural analgesia. Secondary objectives include the evaluation of postoperative pain intensity, opioid consumption, adverse effects, postoperative complications, quality of life, quality of recovery, and patient satisfaction.

**Methods:**

This is a single-center, prospective, randomized, parallel-group clinical trial comparing intercostal cryoanalgesia with thoracic epidural analgesia for postoperative pain control in patients undergoing thoracic surgery. Fifty adult patients (≥18 y) are randomized 1:1 to either epidural or cryoanalgesia groups. All perioperative and postoperative care is provided by the attending clinical teams according to routine institutional practice, with no influence from the research team beyond randomized allocation. The primary endpoint is postoperative hospital length of stay. Secondary outcomes include pain intensity (visual analog scale), opioid consumption, incidence of adverse effects and complications, quality of life (WHOQOL-BREF), and quality of recovery (QoR-15). Data are collected up to 1 year postoperatively.

**Results:**

Approval from the Human Research Ethics Committee was obtained in November 2024, and participant recruitment began in July 2025. Data collection commenced concurrently with participant recruitment and is expected to be completed by August 28, 2027. Data analysis will begin in September 2027, with results anticipated in the first quarter of 2028.

**Conclusions:**

This study protocol outlines a randomized clinical trial designed to assess clinical outcomes associated with intercostal cryoanalgesia compared with thoracic epidural analgesia following thoracic surgery. The findings are expected to contribute to the evidence base on postoperative pain management and inform the design of future comparative and implementation studies in this field.

## Introduction

Thoracic surgery is recognized as one of the most painful surgical procedures due to the extensive trauma to tissues, muscles, ribs, and intercostal nerves. Postoperative pain arises from a combination of nociceptive and neuropathic components and can significantly impair respiratory mechanics, mobility, and postoperative recovery [1,2]. Poorly controlled pain following thoracic surgery is associated with pulmonary complications such as atelectasis and pneumonia, prolonged hospitalization, and increased morbidity [3].

In addition, acute postoperative pain may progress to chronic pain syndromes, underscoring the importance of effective perioperative analgesic strategies [4,5]. Inadequate management of acute postoperative pain is a well-established risk factor for chronic post thoracotomy pain syndrome, a debilitating condition that may persist for months or even years after surgery [6-8]. Effective pain control, is therefore essential, for optimal postoperative recovery, with a direct impact on pulmonary function, mobility, and overall clinical outcomes [9].

Intravenous opioids remain a cornerstone of postoperative pain management; however, their use is associated with adverse effects including respiratory depression, nausea, vomiting, constipation, and dependence [6,10]. Thoracic epidural analgesia is considered the gold standard technique for open thoracotomy and other major thoracic procedures, providing superior analgesia and reduced pulmonary complications compared with systemic opioids [11,12]. Nevertheless, epidural analgesia carries inherent risks, such as hypotension, urinary retention, motor blockade, and potential neurological injury [13,14]. Furthermore, contraindications including coagulopathy and infection limit its applicability in selected patients [15].

Contemporary perioperative care increasingly favors multimodal analgesic strategies that combine systemic and regional techniques to optimize pain control while minimizing opioid exposure. Regional techniques such as intercostal and paravertebral nerve blocks have demonstrated efficacy in thoracic surgery [16,17,18]. However, continuous local anesthetic infusions delivered via indwelling catheters may be associated with complications including infection, catheter displacement, and pump malfunction [19].

Intercostal cryoanalgesia has re-emerged as a promising modality for postoperative pain control in thoracic surgery [20-23]. This technique induces a reversible interruption of sensory nerve conduction by freezing intercostal nerves to extremely low temperatures, typically between −70 °C and −90 °C, using compressed nitrous oxide. The resulting axonal and myelin sheath disruption inhibits nerve transmission while preserving the structural integrity of the endoneurium, perineurium, and epineurium, thereby allowing complete nerve regeneration over several weeks. This mechanism provides prolonged analgesia lasting approximately two months, covering the critical period of postoperative tissue healing, followed by full neural recovery [24-26].

Earlier studies comparing cryoanalgesia with intercostal nerve blocks or thoracic epidural analgesia suggested reductions in opioid consumption and hospital length of stay among patients receiving cryoanalgesia [27,28]. However, these studies were conducted using earlier-generation cryotechnology, limiting their applicability to current surgical practice. Advances in cryoanalgesia equipment, such as digital temperature control and ergonomic probes, have increased the precision and safety of the procedure. Therefore, the efficacy and safety of modern intercostal cryoanalgesia should be reassessed.

In this context, a prospective randomized clinical trial was designed to compare intercostal cryoanalgesia with thoracic epidural analgesia in adult patients undergoing thoracic surgery. The primary objective is to compare postoperative hospital length of stay between the two techniques. Secondary objectives include the evaluation of postoperative pain intensity, opioid consumption, adverse effects, postoperative complications, quality of life, quality of recovery, and patient satisfaction.

## Methods

### Study Design and Setting

This is a single-center, prospective, randomized, parallel-group clinical trial comparing intercostal cryoanalgesia with thoracic epidural analgesia for postoperative pain management in patients undergoing thoracic surgery. The study is conducted at the Thoracic Surgery Division of the Escola Paulista de Medicina, Federal University of São Paulo (UNIFESP), São Paulo, Brazil. Apart from randomization to the analgesic technique, no additional diagnostic or therapeutic interventions are mandated by the study protocol.

### Participants

Eligible participants are adults aged 18 years or older undergoing elective thoracic surgical procedures involving the pleural cavity, including: (1) anatomic lung resections (lobectomy, segmentectomy), (2) wedge resections, (3) pleural procedures, and (4) selected mediastinal surgeries. Surgical approaches include thoracotomy and video-assisted thoracoscopic surgery (VATS). Written informed consent is obtained from all participants prior to enrollment.

Exclusion criteria include procedures not involving access to the pleural cavity, sympathectomy, contraindications to thoracic epidural analgesia (such as coagulopathy or local infection), and cognitive impairment precluding informed consent or reliable pain assessment. Additional exclusion criteria include contraindications to cryoanalgesia, such as prior intercostal nerve injury in the target area, severe peripheral neuropathy, or conditions that may impair nerve regeneration.

### Randomization and Blinding

Participants are randomized in a 1:1 ratio to receive either intercostal cryoanalgesia or thoracic epidural analgesia. Randomization is performed using a computer-generated sequence with variable block sizes and stratification by surgical approach (VATS vs open surgery), prepared by an independent investigator. Allocation concealment is ensured using sequentially numbered, opaque, sealed envelopes opened immediately before surgery.

Stratification by surgical approach was implemented to account for potential differences in postoperative pain trajectories and recovery patterns between minimally invasive and open procedures. However, given the overall sample size, the study is not powered for formal interaction testing, and subgroup analyses will be considered exploratory.

Blinding of surgeons, anesthesiologists, and patients is not feasible due to the nature of the interventions. However, outcome assessors and data analysts remain blinded to group allocation, following a Prospective, Randomized, Open, Blinded Endpoint design to minimize assessment bias.

Given the open-label nature of the study and the inclusion of patient-reported outcomes (eg, pain, quality of life, and satisfaction), there is an inherent risk of reporting bias. To mitigate this limitation, outcome assessors and data analysts will remain blinded to treatment allocation, and standardized validated instruments will be used for all patient-reported measures.

### Interventions

In the control group, thoracic epidural analgesia is performed under aseptic conditions at an intervertebral level between T5 and T8, selected according to the planned surgical incision. The epidural space is identified using the loss-of-resistance technique, and catheter placement will be confirmed with 2% lidocaine. A continuous local anesthetic infusion will be maintained intraoperatively and postoperatively according to institutional protocols. Epidural failures, including inadequate sensory block, refractory hypotension, catheter malposition, or conversion to systemic analgesia, are documented and included in both intention-to-treat and per-protocol analyses.

The epidural analgesic regimen is not strictly standardized, as it follows institutional practice and clinician judgment. While this pragmatic approach enhances external validity, it may introduce variability in analgesic delivery, including the potential use of epidural opioids. This could influence total opioid consumption in the epidural group and will be acknowledged as a potential source of bias in the interpretation of results.

In the experimental group, intercostal cryoanalgesia is performed intraoperatively under direct visualization using the Cryo-S Painless system (Metrum Cryoflex, Poland). The cryoprobe, using pressurized nitrous oxide, achieves a probe-tip temperature of −89 °C and is applied directly to the intercostal nerves corresponding to the surgical incision site, including incision-level nerves and additional levels determined by the distribution of VATS ports, typically encompassing five intercostal levels. Each nerve will undergo a single freezing cycle of 2 minutes. Procedural parameters, including number of treated levels, freeze duration, probe temperature, and distance from the sympathetic chain, are prospectively documented to ensure procedural consistency.

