### Postoperative Care and Follow-Up

All perioperative and postoperative clinical care is provided by the attending surgical and anesthesia teams in accordance with routine institutional practice for thoracic surgery. Decisions regarding analgesic medication selection, dosing, timing, and perioperative management, including preoperative preparation and postoperative care, are made exclusively by the treating physicians based on standard clinical judgment and patient-specific needs. The research team does not influence clinical decision-making beyond the randomized allocation to the analgesic technique under investigation. This approach is intended to reflect real-world clinical practice and to minimize performance and co-intervention biases.

Postoperative management follows standardized institutional protocols routinely used in thoracic surgery in both groups, including a multimodal analgesic regimen consisting of intravenous tramadol (100 mg every 8 h), oral codeine/paracetamol (30 mg every 6 h), or subcutaneous or intravenous morphine (2 mg every 4 h as needed for rescue analgesia). Non-opioid analgesics include dipyrone (1 g every 4‐6 h), paracetamol (500 mg every 6 h), ketoprofen (100 mg every 12 h), and gabapentin (300 mg every 12 h) unless contraindicated. Patient-controlled analgesia is initiated by the attending clinical team when predefined institutional thresholds for insufficient analgesia are met. Postoperative nausea, vomiting, pruritus, and sedation are recorded using standardized criteria. All patients receive respiratory physiotherapy and education regarding safe mobilization and analgesic use. Conversions and crossovers are prospectively documented and accounted for in intention-to-treat and per-protocol analyses.

Hospital discharge is determined by the attending clinical team according to standardized institutional criteria, including adequate pain control (visual analog scale, VAS ≤3 at rest), independent mobilization, stable respiratory status without supplemental oxygen, absence of fever for 24 hours, and chest drain removal according to institutional thresholds. Patients will be discharged with oral analgesics.

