Postoperative follow-up assessments are conducted at one month, three months, and 12 months following the initial procedure. Outcomes include pain intensity (VAS at rest and during mobilization , such as coughing or ambulation), quality of life (World Health Organization Quality of Life – Brief Version, WHOQOL-BREF), quality of recovery (Quality of Recovery-15, QoR-15), physical activity, and postoperative complications. Screening for neuropathic pain (Pain Detection Questionnaire, painDETECT), and chest-wall sensory changes using von Frey monofilaments occur at three and 12 months.

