### Outcomes

The primary outcome is postoperative hospital length of stay, defined as the number of days from surgery to hospital discharge. Secondary outcomes include pain trajectories, cumulative opioid consumption at 48 and 72 hours, time to chest drain removal, postoperative complications, opioid-related adverse effects, quality of recovery, health-related quality of life, chronic post thoracotomy pain at 3 and 12 months, ICU stay, and patient satisfaction. Adverse events are monitored and classified according to the Common Terminology Criteria for Adverse Events.

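### Epidural opioids may enter cumulative opioid consumption as part of the control technique only, and the plan acknowledges this instead of reporting systemic and epidural opioid separately

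*Protocol article*

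**What the plan says.** All references are to the protocol article.

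- **Outcomes** lists "cumulative opioid consumption at 48 and 72 hours" among the secondary outcomes.
- **Interventions** describes the basic control technique: "A continuous local anesthetic infusion will be maintained intraoperatively and postoperatively according to institutional protocols". It then adds "The epidural analgesic regimen is not strictly standardized, as it follows institutional practice and clinician judgment", and says of this pragmatic approach that "it may introduce variability in analgesic delivery, including the potential use of epidural opioids".
- The same section gives the planned handling: "This could influence total opioid consumption in the epidural group and will be acknowledged as a potential source of bias". The acknowledgement belongs to the interpretation of results; no analytic step is attached to it.
- **Postoperative Care and Follow-Up** gives both arms a background that itself contains systemic opioids (tramadol, codeine with paracetamol, or rescue morphine): "Postoperative management follows standardized institutional protocols routinely used in thoracic surgery in both groups, including a multimodal analgesic regimen".
- **Discussion, Overview** concedes that length of stay has many causes, and relies on opioid consumption, with other secondary outcomes, for a more direct view of how well the analgesia works.

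**The concern.** The authors have themselves identified a distortion of a named outcome that arises in one arm. Opioid given through the epidural catheter belongs to the allocated technique. It is not a response to inadequate analgesia, and the cryoanalgesia technique has no counterpart to it. A single total therefore mixes two quantities: what the technique delivers by design, and what patients need on top of it.

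An acknowledgement cannot separate the two after the event. Unless drug, dose and route are held separately, a reader of the results cannot tell whether a difference in the total reflects less need under cryoanalgesia or only the content of the epidural infusion. The outcome would then be least informative where the Discussion relies on it, as a more direct measure than length of stay.

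**Working it through.** The article gives no figure for the opioid outcome, so there is none to reproduce. The sample size (23 per group, 50 enrolled) concerns length of stay and plays no part here. The check is algebraic.

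**Inputs**, all as means over the window in oral morphine equivalents:

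- C = systemic opioid per patient in the cryoanalgesia arm (not stated).
- E = systemic opioid per patient in the epidural arm if the infusion held local anaesthetic only (not stated).
- p = share of the epidural arm given epidural opioid. Interventions says only that such use is possible.
- d = mean epidural opioid dose among those given it (not stated).
- s = mean systemic opioid spared in those patients because of the epidural opioid (not stated; zero or more).

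**Step 1: systemic opioid only.** The epidural-arm mean is E − p·s. The difference, epidural minus cryoanalgesia, is

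(E − C) − p·s.

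**Step 2: systemic plus epidural opioid.** The epidural-arm mean is E − p·s + p·d. The difference is

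(E − C) + p·(d − s).

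**Step 3: the gap between the two definitions.** Step 2 minus Step 1 is p·d. The whole effect of the counting choice is the mean epidural opioid dose per control patient, and it is zero if p = 0.

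**Step 4: equal underlying systemic use (E = C).** The systemic-only difference is −p·s, which is zero or favours epidural. The combined difference is p·(d − s), which favours cryoanalgesia when the epidural dose exceeds what it spares, and equals p·d when nothing is spared. The same data can therefore point in opposite directions according to the definition.

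**Step 5: what can be concluded.** Because p·d cannot be negative, the combined difference in means is never smaller than the systemic one. A cryoanalgesia advantage seen only on the combined total may be no more than p·d. An epidural advantage seen only on the systemic total may be no more than p·s. A difference in the same direction on both totals does not depend on the counting rule. Each total still needs its own interval, because epidural opioid changes the spread in the control arm as well as its mean.

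None of p, d or s can be taken from the article, so no numerical size follows.

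**The case against.** The strongest reply has four parts.

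1. **The issue is disclosed.** The authors name the affected arm and call it potential bias. That is so, but disclosure is also the only handling stated. This is a stated choice, not a detail left to a fuller document.
2. **Total exposure by allocated technique is a legitimate intention-to-treat comparison in a pragmatic trial.** This stands. It is a reason to keep the combined total, and no reason to report it alone.
3. **A systemic-only definition is not neutral either.** This also stands. A reader might infer that the outcome is simply biased towards cryoanalgesia and that excluding epidural opioid removes the bias. The article supports neither step. It fixes no counting rule, and Step 1 shows that a systemic-only total can favour epidural when neuraxial opioid replaces systemic doses.
4. **The stakes are limited.** The outcome is one of several secondary ones, the basic infusion is local anaesthetic, and epidural opioid may be rare or absent. All of this is correct and limits the weight of the point.

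A reader might also infer that discharge cuts the 72-hour window short, because "Patients will be discharged with oral analgesics" and "Postoperative follow-up assessments are conducted at one month, three months, and 12 months following the initial procedure". The article does not say that counting stops at discharge, does not say that the discharge analgesics are opioids, and gives no expected mean stay. Such a rule is also commonly left to the full protocol or analysis plan. At most, if only in-hospital doses are counted, early discharge could lower the 72-hour total in the arm that leaves sooner.

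**Conclusion.** The point holds in a limited form. The article allows epidural opioid in the control technique, recognises that this can alter the opioid total there, and answers with acknowledgement alone. The distortion can run either way: towards cryoanalgesia if epidural opioid is counted and exceeds what it spares, towards epidural if it is left out and spares systemic doses. The gap between the two definitions is p·d, which is unknown because neither the frequency nor the dose of epidural opioid is given, and it may be zero.

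The conclusion assumes only that epidural opioid is sometimes used, as the article allows. It concerns a secondary outcome; the primary analysis and sample size are unaffected. It is worth acting on because the Discussion gives opioid consumption a supporting role, and because separate totals are cheap while patients are still being followed.

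**What to change.** The epidural regimen need not change; the change is to recording and reporting.

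- **Record** epidural opioid drug and dose as a variable separate from systemic opioid. Recruitment began in July 2025, so values for patients already treated would have to come from their charts. If the data form already holds this field, only the reporting rule is new.
- **Report by arm, at 48 and 72 hours:** (a) systemic opioid (intravenous, subcutaneous and oral) in oral morphine equivalents; (b) epidural opioid, with the number of patients given it; (c) the sum of the two.
- **State the rule for interpretation:** opioid sparing is concluded only if it holds on both the systemic and the combined totals. If the two disagree, report that the result depends on how epidural opioid is counted.

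The cost is one form field and one extra analysis. The weak part is the conversion of epidural doses to morphine equivalents, which is approximate, so the factor used should be stated with the combined total.

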### Postoperative Care and Follow-Up

All perioperative and postoperative clinical care is provided by the attending surgical and anesthesia teams in accordance with routine institutional practice for thoracic surgery. Decisions regarding analgesic medication selection, dosing, timing, and perioperative management, including preoperative preparation and postoperative care, are made exclusively by the treating physicians based on standard clinical judgment and patient-specific needs. The research team does not influence clinical decision-making beyond the randomized allocation to the analgesic technique under investigation. This approach is intended to reflect real-world clinical practice and to minimize performance and co-intervention biases.

Postoperative management follows standardized institutional protocols routinely used in thoracic surgery in both groups, including a multimodal analgesic regimen consisting of intravenous tramadol (100 mg every 8 h), oral codeine/paracetamol (30 mg every 6 h), or subcutaneous or intravenous morphine (2 mg every 4 h as needed for rescue analgesia). Non-opioid analgesics include dipyrone (1 g every 4‐6 h), paracetamol (500 mg every 6 h), ketoprofen (100 mg every 12 h), and gabapentin (300 mg every 12 h) unless contraindicated. Patient-controlled analgesia is initiated by the attending clinical team when predefined institutional thresholds for insufficient analgesia are met. Postoperative nausea, vomiting, pruritus, and sedation are recorded using standardized criteria. All patients receive respiratory physiotherapy and education regarding safe mobilization and analgesic use. Conversions and crossovers are prospectively documented and accounted for in intention-to-treat and per-protocol analyses.

Hospital discharge is determined by the attending clinical team according to standardized institutional criteria, including adequate pain control (visual analog scale, VAS ≤3 at rest), independent mobilization, stable respiratory status without supplemental oxygen, absence of fever for 24 hours, and chest drain removal according to institutional thresholds. Patients will be discharged with oral analgesics.

Postoperative follow-up assessments are conducted at one month, three months, and 12 months following the initial procedure. Outcomes include pain intensity (VAS at rest and during mobilization , such as coughing or ambulation), quality of life (World Health Organization Quality of Life – Brief Version, WHOQOL-BREF), quality of recovery (Quality of Recovery-15, QoR-15), physical activity, and postoperative complications. Screening for neuropathic pain (Pain Detection Questionnaire, painDETECT), and chest-wall sensory changes using von Frey monofilaments occur at three and 12 months.

